## Abstract

Diminished ovarian reserve (DOR) is characterized by a decrease in the quantity and quality of oocytes, leading to reduced chances of natural conception and a poorer response to fertility treatments. Along with these reproductive challenges, DOR often causes psychological symptoms such as depression, anxiety, and sleep disturbances, which negatively affect overall well-being and quality of life. Acupuncture has been proposed as a promising complementary therapy for DOR, but the mechanisms through which it exerts its effects are not yet fully understood. This study aims to investigate the effects of acupuncture on ovarian function, psychological well-being, and the central nervous system in women with DOR. We will recruit 42 women with DOR and 21 healthy controls (HCs), randomly assigning DOR patients to receive either verum acupuncture (VA) or sham acupuncture (SA) for 12 weeks. Ovarian function will be assessed using Anti-Müllerian hormone (AMH), antral follicle count (AFC), and follicle-stimulating hormone (FSH). Psychological well-being will be evaluated using the Self-Rating Anxiety Scale (SAS), Self-Rating Depression Scale (SDS), and Self-Rating Scale of Sleep (SRSS). To explore the neurological effects, resting-state functional connectivity (rsFC) of the hypothalamus will be assessed using functional magnetic resonance imaging (fMRI). This research aims to clarify how acupuncture affects the central nervous system, hormonal regulation, and ovarian function in women with DOR. The findings may provide valuable insights for developing evidence-based acupuncture protocols that can improve both reproductive outcomes and quality of life for women with DOR.

## Introduction

Ovarian function is crucial for female fertility, as it produces oocytes and secretes hormones such as estrogen and progesterone (1). Diminished ovarian reserve (DOR), characterized by reduced oocyte quantity and/or quality, presents a significant challenge in reproductive medicine, impacting fertility outcomes. While the concept is widely recognized, its precise definition remains debated (2). Clinically, DOR is often diagnosed by markers such as antral follicle count (AFC) < 5, follicle-stimulating hormone (FSH) > 10 IU/L, or AMH< 0.5–1 ng/mL (3). These physiological changes can manifest as menstrual irregularities (e.g., shortened periods, hypomenorrhea, amenorrhea), infertility, and even perimenopausal symptoms like hot flashes, insomnia, decreased libido, and potentially progress to premature ovarian insufficiency or failure (POI/POF) significantly affecting a woman’s reproductive health and overall well-being (4, 5). DOR also increases the risk of cardiovascular disease, osteoporosis, and mental health issues like insomnia, anxiety and depression compared to women experiencing normal menopause (6). Studies show significantly higher rates of depression and perceived stress in women with the loss of ovarian function as well, impacting their quality of life and productivity, and highlighting the substantial psychological burden associated with DOR (7). The underlying causes of DOR are complex and multifactorial, potentially involving genetic predisposition, oxidative stress, mitochondrial dysfunction, inflammation, and fibrosis, all of which impact the ovarian microenvironment (7, 8). This complexity, coupled with the limitations of current diagnostic markers for early detection, makes effective prevention and treatment of DOR challenging.

DOR is a heterogeneous disorder with diverse clinical manifestations that not only impair fertility but also cause menstrual irregularities and perimenopausal symptoms (e.g., insomnia, anxiety, depression, and cognitive dysfunction) (9). Compelling evidence reveals a bidirectional relationship between DOR and psychological distress - approximately 50% of DOR patients exhibit significant depressive symptoms, anxiety, and emotional dysregulation, which may exacerbate DOR progression through hypothalamic-pituitary-gonadal axis dysfunction (10). This neuroendocrine-psychological interplay underscores the mutual reinforcement between DOR and mood disorders, with potential central nervous system consequences. Previous studies have suggested that abnormalities in the hypothalamic-pituitary-ovarian (HPO) axis may be a potential underlying cause of DOR (11). Dysregulation at any point of this axis, whether at the hypothalamic, pituitary, or ovarian level, can disrupt the normal hormonal signaling required for optimal ovarian function, leading to a reduction in the quantity and quality of oocytes (12). Such dysfunction may result from various factors, including endocrine disorders, genetic predispositions, or environmental influences, which can ultimately contribute to the pathogenesis of DOR (13). HPO axis is critical for the maintenance of mental and physical health (14). Understanding these disruptions in the HPO axis may offer new insights into the mechanisms driving DOR and pave the way for more effective diagnostic and therapeutic approaches. In recent decades, the advent of noninvasive functional magnetic resonance imaging (fMRI) has provided unprecedented insights into brain activity, enabling the exploration of central physiological processes with remarkable precision. This advanced imaging technique has revolutionized our ability to investigate the dynamic neural mechanisms underlying a wide range of mental, physical, and emotional functions, thus significantly enhancing our understanding of brain function in both health and disease (15–17).

DOR patients might suffer from chronic estrogen deficiency, hormone replacement therapy (HRT) is one of the most widely used treatment (18). This treatment approach seeks to relieve symptoms and restore hormone levels to a physiologically normal range, but it also comes with potential drawbacks, such as increase the risk of ovarian cancer (19). Platelet-rich plasma (PRP) is another promising treatment that has shown the potential to promote endometrial and follicle growth for restoring female reproductive and endocrine function, while the results shows that it do not improve IVF outcomes in women under 38 and lack of standardization (20, 21). Given this context, there is an urgent need for an effective treatment for DOR. Acupuncture is a traditional Chinese medical (TCM) approach involves treating patients by stimulating specific acupoints on the body to regulate the flow of Qi and blood within the meridian system. For decades, acupuncture has found extensive application in the treatment of a diverse array of physical or mental diseases, encompassing conditions like infertility, ovarian insufficiency, menstrual cycle irregularity, insomnia, and depression (6, 22–24). Acupuncture has been widely used to treat DOR, and has demonstrated curative effects (25, 26). Also, acupuncture could modulate homeostasis of HPO axis (27). However, due to a lack of high-quality evidence supporting its use and insufficient elucidation on the mechanisms underlying acupuncture’s effects.

In another study protocol designed to evaluate the effects of acupuncture on menstrual regulation and pregnancy enhancement in patients with DOR, enrolled only DOR patients with verum acupuncture (VA) treatment and compared the related changes in brain functional network and other indicators of ovarian function (28), which didn’t consider the placebo effect, and its potential clinical relevance. Sham acupuncture (SA) serves as a placebo control in acupuncture clinical trials, designed to elucidate both specific and nonspecific components pertinent to acupuncture therapy (29, 30). There is still controversy regarding site-specificity in acupuncture, some authors have suggested that SA interventions were not totally inert, often being associated with moderately large non-specific effects (31). When VA is compared with SA, different cerebral responses are observed, which may explain the favorable effects of VA in clinical studies on pain treatment (32). Various approaches have been employed to mimic SA, some studies have adopted simulated needling procedures, which potentially exert effects akin to acupressure, while others have utilized superficial needling at non-acupoints or incorrect acupoints based on traditional theories (29). Penetrating SA may induce additional clinical treatment effects and influence brain function, potentially confounding the results. Therefore, in this study, we will use non-penetrating sham devices to minimize nonspecific effects and more accurately simulate the specific clinical efficacy of VA.

In this study, we aim to assess the impact of acupuncture on HPO axis-related brain function and the relationship between homeostasis of HPO axis and sleep quality, depression, and anxiety in patients with DOR.

## Materials and methods

### Study design

This study will consist of two experiments: a cross-sectional experiment and a longitudinal experiment (**Figure 1**). The cross-sectional experiment will examine brain functional connectivity (FC) in patients with DOR by comparing seed-based FC between DOR patients and healthy controls (HCs). The longitudinal experiment will investigate the clinical efficacy of acupuncture and its underlying neurological mechanisms by comparing FC before and after treatment. Additionally, we will compare the differences in FC and clinical symptoms, such as ovarian function, anxiety, depression, and sleep disturbances, between the VA and SA groups following treatment. Finally, we plan to analyze the relationship between changes in FC and clinical symptoms. This will allow us to investigate whether acupuncture can modulate hypothalamic FC and subsequently improve clinical symptoms in DOR patients. The longitudinal acupuncture experiment was approved by the Ethics Committee of Sir Run Shaw Hospital Zhejiang University School of Medicine (2025YL0012) and submitted to the International Traditional Medicine Clinical Trial Registry (ITMCTR2025000576). All participants will be provided written informed consent before the initiation of any study procedures. The study adhered to the CONSORT guidelines for reporting

**Figure 1 f1:**
[figure not shown]
1 Trial flow chart.

### Participants

We plan to recruit 42 patients with DOR and 21 healthy female volunteers of childbearing age through WeChat, poster postings, and other channels. A dedicated staff member will be responsible for patient recruitment and will meticulously record each participant’s information, which will be documented in the Case Report Form (CRF). The recruitment materials will include detailed contact information. This study adheres to the principles outlined in the Declaration of Helsinki.

Inclusion criteria for healthy controls:

Age between 20 and 40 years (inclusive).Normal gynecological ultrasound, normal hormone levels, and regular menstrual flow with normal color and quantity.No severe heart, liver, kidney, or hematologic system disorders.Right-handed.Voluntary participation in the trial and signed informed consent.

The inclusion criteria for DOR are similar to our previous design (23):

Age between 20 and 40 years (inclusive).Diagnosis of DOR based on the 2016 POSEIDON criteria and the 2020 expert consensus on the treatment of low-prognosis populations in assisted reproductive technology using the Delphi method in China.AMH level < 1.2 ng/ml.AFC < 5 (Note: AFC should be measured on days 2–3 of the menstrual cycle, with at least a 4-week interval between two measurements).Fertility desire, with plans for natural conception or, as assessed by a reproductive specialist, plans to undergo controlled ovarian stimulation with an antagonist protocol in the next *in vitro* fertilization (IVF) and embryo transfer cycle.Right-handed.Voluntary participation in the trial and signed informed consent.

Exclusion criteria:

Coexisting conditions that affect fertility, including congenital reproductive organ abnormalities, untreated endometrial polyps, untreated uterine infections, untreated tubal hydrosalpinx, thin endometrium, uterine fibroids, endometriosis, or other organic diseases.Coexisting polycystic ovary syndrome (PCOS).Coexisting untreated hyperprolactinemia, hyperandrogenism, thyroid dysfunction, chronic adrenal insufficiency, or other metabolic and endocrine disorders.Acupuncture treatment for fertility enhancement received within the last three months.Plans for *in vitro* fertilization (IVF-ET) within 2 months after enrollment.Vulnerable populations other than illiterate individuals, including those with mental illness, cognitive impairments, critically ill patients, pregnant women, etc.

Regular reminders via WeChat or telephone will be used to improve participant adherence. If any of the following events occur in the enrolled patients, their intervention will be terminated forcibly:

Serious complications or other significant illnesses that require emergency measures.Pregnancy;Withdrawal of informed consent for any reason. There is no post- trial intervention or care for patients in this trial.

No treatment will be given to healthy group, only one fMRI, laboratory test and neuro-psychological test will be performed at baseline.

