### Acupuncture interventions

Eligible participants will be randomly allocated into the VA or SA group at a 1:1 ratio via the web-based response system of the Central Randomisation System for Clinical Research. Stratified randomization will be applied, with age (35 years) as the stratification factor. Unblinding will not be required during the study as it will not have clinical relevance to treatment decisions. The randomization plan will be generated using the “Proc plan” procedure in SAS 9.3 statistical software (SAS Institute Inc., Cary, NC, USA), and all related parameters set during the randomization process will be stored in a blinded database. When eligible participants are enrolled, the randomization number will be assigned by the responsible personnel or researcher through phone or online access to the central randomization system. The random distribution cards will contain random numbers, serial numbers, and groups, packed in opaque numbered envelopes. The envelope will be unsealed following study enrolment. Owing to the particularity of acupuncture research, it is difficult to blind the acupuncture operators. As such, fake acupuncture devices and separate treatment rooms will be used for each patient to blind them as much as possible. Moreover, the “three separations strategy” will be strictly adhered to by researchers, operators, and statisticians throughout the research process. Efficacy evaluation, data analysis, and statistics will be completed by third parties blinded to the groupings.

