### Demographic and clinical data analyses

Demographic and clinical outcome analyses will be conducted using SPSS 22.0 software. In the cross-sectional study, two-sample t-tests and Chi-square tests will be employed to compare baseline characteristics between the DOR patient group and HCs. In the longitudinal study, paired t-tests will be used to compare changes in clinical symptoms (SAS, SDS, and SRSS scores) and laboratory test results (AFC, FSH, and AMH) within each group before and after treatment. Subsequently, a two-way analysis of variance (ANOVA), with time as the within-subject factor, will be applied to examine differences in clinical symptoms between the VA and SA groups before and after treatment. A *p*-value of < 0.05 will be considered statistically significant.

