### MRI data preprocessing

Preprocessing of MRI images will be conducted using the DPARSF (http://rfmri.org) and SPM 12 (www.fil.ion.ucl.ac.uk/spm) toolkits within MATLAB 2014b (MathWorks, Natick, MA). The preprocessing pipeline will include the following steps: (1) removal of the first 10 volumes; (2) slice timing correction; (3) realignment of images to correct for head motion; (4) co-registration of T1-weighted images with functional images; (5) normalization of T1 images to Montreal Neurological Institute (MNI) space, followed by segmentation into gray matter, white matter, and cerebrospinal fluid; (6) spatial smoothing of the images using an isotropic Gaussian kernel with a full width at half maximum (FWHM) of 6 mm; (7) temporal bandpass filtering (0.01-0.08 Hz); and (8) regression of nuisance signals, including global mean, white matter, cerebrospinal fluid signals, and six motion parameters. Considering the aim is to estimate the relationship between ovarian and brain and the hypothalamic-pituitary-ovarian (HPO) axis, the region of interest (ROI) will be selected as the hypothalamus. For static functional connectivity (FC) analysis, Pearson’s correlation coefficients between the reference time series of each seed and the time series of all brain voxels will be computed. These coefficients will then be transformed into z-scores using Fisher’s z-transformation to enhance normality (24). Two-sample t-tests will be conducted to identify significant differences in FC between the DOR and healthy control (HC) groups, with age and mean framewise displacement (FD) as covariates. Moreover, Kisspeptin is a key regulator of gonadotropin secretion and is primarily located in the rostral preoptic area and the infundibular nucleus of the human hypothalamus (37). In this study, we will refer to the segmentation method described in Ogawa (38) to perform subregion segmentation of the hypothalamus in our subjects, with a particular focus on the rostral preoptic area and the infundibular nucleus, as well as the whole-brain FC. For the longitudinal analysis, paired t-tests will be used to compare within-group statistical maps, while a two-way analysis of variance (ANOVA) will be applied to compare between-group statistical maps. Multiple comparisons will be corrected for using a threshold of *p* < 0.05 at the voxel level and *p* < 0.05 at the cluster level, with false discovery rate (FDR) correction.

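### Outside the FC maps, the DOR versus healthy-control comparison is unadjusted for age, so a difference in the scales or FSH could partly reflect age

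*Protocol article*

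**What the plan says.** **Recruitment.** Under Participants: "We plan to recruit 42 patients with DOR and 21 healthy female volunteers of childbearing age". The patient list and the control list carry the same age criterion, "Age between 20 and 40 years (inclusive"), and both require right-handedness. No other alignment of the two groups on age is stated.

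**Age elsewhere in the design.** Under Acupuncture interventions: "Stratified randomization will be applied, with age (35 years) as the stratification factor". This governs allocation of patients to verum or sham acupuncture. Controls are not randomised, so it does not involve them.

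**What is measured in controls.** Under Participants, for the healthy group: "only one fMRI, laboratory test and neuro-psychological test will be performed at baseline". Table 2 ticks AFC, FSH and AMH, the three scales and MRI for controls at baseline.

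**How the groups are compared.** Two methods are given:
- For the FC maps (MRI data preprocessing), a two-sample t-test "with age and mean framewise displacement (FD) as covariates".
- Otherwise (Demographic and clinical data analyses), "two-sample t-tests and Chi-square tests will be employed to compare baseline characteristics between the DOR patient group and HCs". No covariate is named, and the significance threshold in that section is p < 0.05.

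**Purpose.** Study design defines the cross-sectional experiment as "comparing seed-based FC between DOR patients and healthy controls (HCs"). The Discussion adds that relationships between brain function, ovarian markers and the scales will be examined in patients and controls at baseline.

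**The concern.** By putting age into the FC model, the authors treat it as a possible confounder between patients and controls. The same two groups of women are compared on everything else without it.

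An age gap is plausible. Patients are selected on low AMH, low AFC and a wish to conceive. Controls need normal hormones and ultrasound, and have no fertility criterion. Nothing beyond a 20-year range brings their ages together.

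The Introduction argues that DOR carries a burden of anxiety, depression and poor sleep. A significant baseline difference in SAS, SDS or SRSS would readily be read as support for that. If the groups differ in age and the scale varies with age, part of the difference is not due to DOR. The bias can also run the other way and hide a real difference.

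The point bears mainly on the three scales and on FSH. AMH and AFC separate the groups by the entry criteria themselves, and age adjustment would not change that. FSH is partly in the same position, since controls must have normal hormone levels.

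**Working it through.** The article has no figure of its own to reproduce here: 21 per group is set by convention in imaging studies, without an effect size, SD or power. The check therefore asks how far an unadjusted t-test departs from 5% when DOR has no effect and the groups differ in age.

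**Inputs from the article:** n = 42 patients and 21 controls; threshold 0.05, taken as two-sided because sidedness is not stated.

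**Assumed inputs, none given in the article:** an age gap g in units of the within-group age SD; a within-group correlation r between age and outcome; a linear age effect; no true DOR effect.

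**Step 1, spurious difference.** In outcome SDs, shift = r × g.

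**Step 2, non-centrality.** The standard error in SD units is √(1/42 + 1/21) = √0.0714 = 0.267, so ncp = r × g / 0.267, with 42 + 21 − 2 = 61 degrees of freedom.

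**Step 3, false-positive rate** from the non-central t distribution:

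| Gap g (SD) | Correlation r | Shift (SD) | ncp | False-positive rate |
|---|---|---|---|---|
| 0 | any | 0 | 0 | 5.0% |
| 0.5 | 0.2 | 0.10 | 0.37 | 6.6% |
| 1.0 | 0.2 | 0.20 | 0.75 | 11.4% |
| 1.0 | 0.3 | 0.30 | 1.12 | 19.7% |
| 1.5 | 0.3 | 0.45 | 1.68 | 38.1% |

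**Step 4, effect of the covariate.** With an assumed age SD of 5 years, gaps of 3, 5 and 8 years and correlations of 0.2, 0.3 and 0.5 were simulated, 4,000 runs each. For a gap of 5 years (1 SD) and r = 0.3, the unadjusted test rejected in 19.6% of runs, in agreement with Step 3. A linear model with group and age rejected in 4.8% to 5.4% of runs across all nine scenarios. Age adjustment thus restores the nominal level where the age effect is linear, as simulated.

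**The case against.** The strongest reply is that the cross-sectional experiment, as Study design defines it, is the FC comparison, and that test is adjusted for age. This stands, and it confines the point to secondary comparisons.

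A second reply is that the unadjusted tests are described as a comparison of baseline characteristics. The sentence does not name the scales; they appear in the next sentence, on within-group changes. A baseline table is conventionally unadjusted and, if age is listed, would show an imbalance. This stands in part. That the scales will be compared between patients and controls is an inference, though a likely one, since controls complete them and no other DOR-HC test for them is described. A table that reveals an age gap does not correct for it.

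Third, the magnitudes are assumed. That is so, and the mildest case with a gap is close to nominal.

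A reader might go further and infer that the FC model is itself inadequate because the ages barely overlap or the adjustment is only linear. The article does not support this. Both groups span 20 to 40, and a linear term over that range is ordinary practice. The loss of precision is modest. With a gap of 1 SD the variance inflation is 1 + (1/3)(2/3) × 1² = 1.22, so the standard error rises by a factor of 1.106. If age also correlated 0.3 with FC, the residual SD would fall by √(1 − 0.09) = 0.954, and the net factor would be about 1.055.

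A reader might also infer that the controls must be age-matched. Recruitment quotas are a detail that a condensed article may leave to the full protocol, so their absence is not an error. Balancing only at age 35 would also leave a wide band, 20 to 35, in which ages could differ.

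**Conclusion.** The point holds in a limited form and is minor. The article states a method for each of the two DOR-HC comparisons, adjusts one for age and leaves the other unadjusted. A difference between patients and controls in SAS, SDS, SRSS or FSH could therefore partly reflect age.

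The false-positive rate ranges from 5% with no age gap, through about 7% (0.5 SD, r = 0.2), to about 20% (1 SD, r = 0.3). A gap of 1.5 SD with r = 0.3 would give 38%, but nothing in the article shows that such a gap is to be expected. All these figures rest on an assumed gap, correlation and linear age effect.

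It does not follow that the cross-sectional experiment as a whole is confounded by age: the FC comparison carries the covariate. The randomised verum-sham comparison does not involve the controls and is unaffected.

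**What to change.** In Demographic and clinical data analyses, state that SAS, SDS, SRSS and FSH will be compared between DOR patients and healthy controls in a linear model with group and age, as already planned for FC. State also that any unadjusted table of baseline characteristics is descriptive and will not be read as evidence of an effect of DOR.

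The cost is a sentence or two of wording. Age is already needed for eligibility and for the FC model, so no new data are required, and neither the sample size nor recruitment changes.

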### Clinical outcome measurement

The AFC will be measured via transvaginal ultrasonography on days 2–5 of the menstrual cycle. AFC, along with serum levels of basal FSH and AMH, will be assessed at three time points: baseline (week 0), post-treatment (week 12), and 12-week follow-up (week 24).

The neuro-psychological test such as SAS, SDS, and SRSS will be used for clinical assessments at three time points: baseline (week 0), post-treatment (week 12), and 12-week follow-up (week 24).

The time points for each test in two group is listed in **Table 2**.

**Table 2 T2:** Time points for each test in two groups .

Measurements	Baseline		12 weeks		24 weeks	
	DOR	HC	DOR	HC	DOR	HC
AFC, FSH, AMH	✓	✓	✓		✓	
AFC	✓		✓			
SAS, SDS, and SRSS	✓	✓	✓		✓	
MRI	✓	✓	✓			

Diminished ovarian reserve, DOR; healthy control, HC; anti-Müllerian hormone, AMH; antral follicle count, AFC; follicle-stimulating hormone, FSH; self-rating anxiety scale, SAS; self-rating depression scale, SDS; self-rating scale of sleep, SRSS; magnetic resonance imaging, fMRI.

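### Within-arm paired t-tests on AFC and AMH can show improvement by regression to the mean if week 0 is a qualifying reading, and the analysis section does not clearly give these markers a between-arm test

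*Protocol article*

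**What the plan says.** **Entry** (Protocol article, Participants). The criteria for women with DOR include "AMH level < 1.2 ng/ml" and a low AFC: "AFC < 5 (Note: AFC should be measured on days" 2–3 of the cycle, "with at least a 4-week interval between two measurements"). The note does not say whether both counts must be below 5, whether both precede treatment, or which one is the baseline.

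**Schedule** (Clinical outcome measurement). AFC, FSH and AMH "will be assessed at three time points: baseline (week 0), post-treatment (week 12), and 12-week follow-up (week 24"). Neither the text nor Table 2 shows a separate screening point. The cycle-day window differs from the one at entry: "The AFC will be measured via transvaginal ultrasonography on days 2–5 of the menstrual cycle".

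**Within-arm test** (Demographic and clinical data analyses). In each group, "paired t-tests will be used to compare changes in clinical symptoms (SAS, SDS, and SRSS scores) and laboratory test results (AFC, FSH, and AMH"), at p < 0.05.

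**Between-arm test** (same section). The two-way ANOVA "will be applied to examine differences in clinical symptoms between the VA and SA groups before and after treatment". One sentence earlier, the section lists the three scales as the clinical symptoms and AFC, FSH and AMH as laboratory results. Study design, by contrast, counts ovarian function among the clinical symptoms to be compared between verum acupuncture (VA) and sham acupuncture (SA).

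**The concern.** Two of the three ovarian outcomes, AFC and AMH, are also entry criteria with an upper limit. A reading accepted because it is low contains, on average, a downward measurement error, and the next reading does not repeat that error. If the accepted reading is also the before value, the expected change is positive with no treatment effect, and the paired t-test tests a null hypothesis that selection has already made false. FSH has no numerical entry limit in the listed criteria, so the argument does not reach it directly.

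A significant rise in follicle count after acupuncture, and after sham, could then be reported in women whose ovarian reserve has not changed. The sham arm would expose this only if the two arms are compared, and for these markers the analysis section leaves that comparison unclear.

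**Working it through.** **Plan's own figure.** The 21 per arm rests on precedent for imaging studies, with no effect size, SD or power, so there is nothing to recompute beyond 42/2 = 21.

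**Inputs from the protocol.** AFC < 5; AMH < 1.2 ng/ml; n = 21 per arm; alpha 0.05, taken as two-sided because sidedness is not stated. The nominal chance of a significant rise is therefore 2.5%.

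**Assumptions, not in the protocol.** AFC = stable true value + independent visit error, rounded to whole follicles and floored at zero. Mean/SD of AFC among the women screened: 4/2, 5/2.5 or 6/3, with 8/4 as an extreme. Between-visit correlation ρ: 0.6 to 0.9. No treatment effect.

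**Expected drift by formula.** For one count that both qualifies and serves as baseline, with a normal approximation and cut c = 4.5:

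drift = (1 − ρ) · SD · φ(z)/Φ(z), where z = (c − mean)/SD.

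For mean 6, SD 3: z = (4.5 − 6)/3 = −0.5, and φ/Φ = 0.352/0.309 = 1.14.
- ρ = 0.8: 0.2 × 3 × 1.14 = 0.68 follicles (simulation 0.71).
- ρ = 0.6: 0.4 × 3 × 1.14 = 1.37 follicles (simulation 1.40).

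**Simulated paired t-test**, t = mean change/(SD of change/√21), counted as a significant rise when t > 2.086 (20 df). Each cell gives mean drift in follicles and the share of arms with a significant rise:

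| Mean/SD, ρ | One gated count is baseline | Two gated counts, last is baseline |
|---|---|---|
| 4/2, 0.9 | 0.16; 11% | 0.09; 6% |
| 4/2, 0.6 | 0.55; 29% | 0.40; 18% |
| 5/2.5, 0.8 | 0.50; 30% | 0.31; 14% |
| 6/3, 0.8 | 0.71; 42% | 0.44; 20% |
| 6/3, 0.6 | 1.40; 74% | 0.96; 45% |
| 8/4, 0.6 (extreme) | 2.28; 92% | 1.53; 67% |

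With a baseline count not used for entry, the drift is 0.00 and the rate of significant rises is 2.4% to 2.8% in every setting.

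**Another noise model.** Log-normal true AFC (median 3 to 5) with either normal cycle noise of SD 0.7 to 1.5 follicles or Poisson noise gives 6% to 74% with one gated count and 5% to 54% with two.

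**AMH.** Log-normal, median 1.0 or 1.5 ng/ml, log-SD 0.7 or 0.8, ρ 0.8 to 0.95, with the qualifying value as baseline: drift 0.03 to 0.21 ng/ml, significant rise in 8% to 42% of arms.

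**Between-arm test.** A two-sample t-test on change, which equals the group-by-time term of a two-group, two-time ANOVA, rejects in 4.5% to 5.5% of null trials under every baseline rule.

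**The case against.** The strongest reply is that the premise is an inference. The entry note mentions two counts at least four weeks apart, and the entry and outcome windows differ (days 2–3 against 2–5), which fits separate readings at least as well as a shared one. Table 2 is an outcome schedule in a condensed article and is irregular (AFC appears in two rows, only one of them with a week-24 tick), so the absence of a screening column is weak evidence. If the first count qualifies and the second is an ungated week-0 value, AFC has no bias. This stands: a reader might infer that the qualifying count certainly is the baseline, and the protocol does not support that. It does not say the opposite either. Two counts that must both be below 5 is also a plausible reading, and it reduces the bias without removing it. For AMH no second pre-treatment measurement is mentioned.

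The second reply is that regression to the mean is equal in expectation in both randomised arms, and the study calls itself exploratory. This also stands. A reader might infer that the trial could falsely favour VA over SA by this route; the simulation shows it would not. What remains is that the analysis section, read literally, gives AFC, FSH and AMH the paired test alone, and the Discussion speaks of demonstrating improvement on markers that include AMH and AFC.

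The third reply is that the magnitude rests wholly on assumed variability. That is correct, and the width of the range reflects it.

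**Conclusion.** The concern holds conditionally. If the week-0 AFC is a gated reading (one count below 5, or two counts both below 5), the within-arm paired t-test exceeds its nominal error. For assumed screening means of 4 to 6 and visit correlations of 0.6 to 0.9, a false significant rise occurs in about 11% to 75% of arms with one gated count and 6% to 45% with two, against 2.5%. AMH is affected less. If week 0 is an ungated reading, the excess disappears. The protocol does not settle which case applies, and the figures depend on variability that it does not give.

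The VA-versus-SA comparison is unbiased in every case. The firm defect is therefore in the analysis section: a test open to this bias is assigned explicitly to AFC and AMH, while the sound comparison is promised for ovarian function in Study design but worded for clinical symptoms only where the tests are specified.

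**What to change.** In Demographic and clinical data analyses:
- Name the VA-versus-SA comparison as the efficacy test for AFC, FSH and AMH, either by the group-by-time term or by ANCOVA on the baseline value. This also brings the section into line with Study design.
- Label the within-arm paired t-tests descriptive, and draw no efficacy statement from them.

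In Participants and Clinical outcome measurement:
- State which AFC and which AMH reading is week 0, and whether it was used for entry.
- Where a second pre-treatment AFC is already taken and is not itself an entry criterion, use it as the baseline whatever its value.
- Reconcile the two AFC cycle-day windows.

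The cost is wording in three sections, with no change to the entry rule and no new visit. A separate ungated AMH baseline would need an extra blood sample; the fix does not require one, because the between-arm test is valid without it. The downside is that within-arm changes can no longer support a claim of improvement.
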